## Abstract

**Background:**

The association between pulmonary tuberculosis (PTB) and diabetes mellitus (DM) has been previously attracted much attention. Diabetes alters immunity to tuberculosis, leading to more frequent treatment failure in TB patients with DM. Moreover, TB and DM often coincide with micronutrients deficiencies, such as retinol and vitamin D, which are especially important to immunity of the body and may influence pancreas β-cell function. However, the effects of retinol and vitamin D supplementation in active TB patients with diabetes on treatment outcomes, immune and nutrition state are still uncertain. We are conducting a randomized controlled trial of vitamin A and/or D in active PTB patients with DM in a network of 4 TB treatment clinics to determine whether the supplementation could improve the outcome in the patients.

**Methods/design:**

This is a 2×2 factorial trial. We plan to enroll 400 active PTB patients with DM, and randomize them to VA (2000 IU daily retinol); VD (400 IU daily cholecalciferol); VAD (2000 IU daily retinol plus 400 IU cholecalciferol) or control (placebo) group. Our primary outcome measure is the efficacy of anti-tuberculosis treatment and ameliorating of glucose metabolism, and the secondary outcome measure being immune and nutrition status of the subjects. Of the first 37 subjects enrolled: 8 have been randomized to VA, 10 to VD, 9 to VAD and 10 to control. To date, the sample is 97.3% Han Chinese and 91.9% female. The average fasting plasma glucose level is 12.19 mmol/L.

**Discussion:**

This paper describes the design and rationale of a randomized clinical trial comparing VA and/or VD supplementation to active pulmonary TB patients with DM. Our trial will allow rigorous evaluation of the efficacy of the supplementation to active TB and DM therapy for improving clinical outcomes and immunological condition. This detailed description of trial methodology can serve as a template for the development of future treatment scheme for active TB patient with DM.

**Trial registration:**

ChiCTR-TRC-12002546

## Background

The merging epidemics of pulmonary tuberculosis (PTB) and diabetes mellitus (DM) and their synergistic role in causing human disease has been attracted much attention [1]. In China, where there are experiencing incredible increase in DM prevalence, an age standardized prevalence of diabetes of 9.7% (10.6% in men and 8.8% in women) and prevalence of pre-diabetes as 15.5% (16.1% in men and 14.9% in women) [2], also a high burden of PTB exists. The combination of tuberculosis and diabetes mellitus and double burden of TB and DM represent a big health threat, which make the treatment failure more frequent and result in more community acquired TB infection. Diabetes alters immunity to tuberculosis, which will lead to higher mycobacterial burden and longer time to culture conversion with treatment, and a higher rate of relapse might result. In studies assessing time to sputum-culture conversion, diabetic patients seem to take longer time to achieve culture negativity. Guler et al. reported that patients with diabetes who received tuberculosis treatment had longer sputum-culture conversion times than non-diabetic patients (67 *vs* 55 days; p=0.02) [3]. Similarly, Restrepo et al. [4] used survival analysis to measure time to culture conversion, and found median time to culture negativity was significantly longer in diabetic patients than that in controls. Radiographic findings in tuberculous patients with diabetes differ from pure TB patients. It was widely believed that pulmonary tuberculosis patients with diabetes presented with an atypical radiographic pattern and distribution and lower lung field tuberculosis was seen more frequently in TB patient with DM. Overlapping toxicities and various drugs used may worse diabetic control and alter the pharmacokinetics of antituberculosis drugs, which makes the clinical treatment of TB patients with DM more difficult.

TB and diabetes often coincide with malnutrition. TB patients frequently suffer from deficiencies of nutrients, such as vitamins A and D, which are fundamental to the integrity of the immune response, especially the host immune response toward Mycobacterium. Studies have shown that vitamin A has an immune protection role against human tuberculosis. In addition, vitamin A supplementation results in a modulation of the immune response in patients with tuberculosis [5,6]. The classic role of vitamin D in the regulation of calcium and phosphate metabolism, and its effects on bone health, have been well established. More recently, a critical role of vitamin D in immunity, respiratory health and insulin resistance has been proposed [7,8]. Low serum vitamin D has been discovered to be associated with higher risk of active tuberculosis. Researches revealed that vitamin D plays a key role in the production of a molecule called cathelicidin, which kills the mycobacterium tuberculosis organism [9,10]. Furthermore, a double-blind randomized controlled trial conducted in 192 healthy adult TB contacts in London discovered that a single oral dose of 2.5 mg vitamin D significantly enhanced the ability of participants' immunity to mycobacteria [11]. However, a trial in Guinea-Bissau found no effect of vitamin D (100,000 IU of cholecalciferol at inclusion and again 5 and 8 months after the start of treatment) on clinical outcome and mortality in patients with TB [12].

Furthermore, vitamins play an important role in glucose metabolism. It has been reported that vitamin D can regulate the β cell function in pancreatic islet, the insulin activity and the systematic inflammation level. Plasma 25(OH) D levels are positively association with both β-cell function and insulin sensitivity [13]. A trial carried out in USA found that in adults at risk of type 2 diabetes, short-term supplementation with cholecalciferol improved β cell function and had a marginal effect on attenuating the rise in Hb A(1c) [14]. Also, Vitamin A and its metabolites, retinoids, have emerged as key participants in the mechanisms of regulation of cellular metabolisms and energetics, which may also play a key role in the process of glucose metabolism.

We designed this VA/D supplementation trial to test the efficacy of micronutrient intervention on active TB patients with DM. We are implementing this randomized controlled trial in a network of TB therapy clinics that offer TB treatment by primary care providers, including standard DM treatment. The primary objective of our trial is to determine whether VA, VD or VAD supplementation is efficacious on anti-tuberculosis treatment and insulin resistance. The secondary objective is to investigate the underlying mechanism including immunological function, nutritional status, etc. We here provide a detailed methodological description of this trial, which can serve as a template for other investigators designing the comprehensive treatment of TB and DM. In addition, we discuss the efficacy of VA and/or VD supplementation on TB and DM to guide future clinical treatment. Finally, we report baseline characteristics of our recruited study population.

## Methods/design

### Study setting

The VA/D supplementation trial is being conducted in a network of 4 TB clinics in Qingdao and Linyi city in Shandong province in China. Together, these clinics provide care for approximately 5,000 active pulmonary tuberculosis patients per year and nearly 10% have DM. These four clinics are the sites for study recruitment, delivery of the VA and/or VD intervention, and all research visits.

VA and/or VD supplementation is delivered by the physicians, together with the nurses, social workers to take care of the patients. The medical team provides comprehensive medical care, including TB and DM pharmacotherapy.

### VA/D supplementation scheme

This is a 2-by-2 factorial-design intervention trial. Active pulmonary tuberculosis patients with diabetes mellitus are offered onsite TB and DM evaluation and treatment by primary care providers, and are free to choose whether to receive VA/D supplementation. Primary care providers receive special training by the project team, including the related knowledge of TB and DM, especially the association between TB and DM; the related nutritional deficiencies and the role of micronutrients in cell-mediated immunity.

Once sign the informed consents, the patients will be randomly assigned to VA (2000 IU daily retinol on top of normal pharmacotherapy) or VD (400 IU daily cholecalciferol on top of normal pharmacotherapy) or VAD (2000 IU daily retinol plus 400 IU daily cholecalciferol on top of normal pharmacotherapy) or control (placebo on top of normal pharmacotherapy) group.

#### Trial inclusion and exclusion criteria

Potential trial subjects are eligible for inclusion if they are affected with active pulmonary tuberculosis and have fasting plasma glucose (FPG) of ≥126 mg/dL or 2-hour glucose level of 200 mg/dL or above by OGTT; have no history of previous anti-tuberculosis treatment and oral hypoglycemic drugs or insulin used; plan to initiate onsite anti-tuberculosis and DM treatment at the TB clinic within the next six months; attend their TB clinic after hospitalization once or twice per month to receive supplementation pill and physical examination; plan to stay in local place for 2 years. Participants are excluded if they are unable or unwilling to provide informed consent; are drug resistant at baseline or during the follow up; pregnancy; lactation; use of corticosteroids or supplements containing vitamin A or vitamin D during the previous month; chronic renal failure as indicated by elevated serum uric acid or creatinine concentrations; and clinical signs of neoplasm and congestive heart failure.

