### Baseline assessment

The baseline assessment consists of an interview and physical measurement. Baseline fast blood glucose, results of urine toxicology tests, liver function test and other related clinical indexes are obtained by chart review. The baseline interview is conducted prior to vitamin supplementation initiation, and at this visit all subjects are invited to attend VA/D supplementation trial. Following completion of the baseline assessment, participants receive their assignment to one of the four arms.

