### Visit schedule and measures

Frequency and length of research visits during the 24 to 32 weeks (according to the anti-tuberculosis drug treatment period) intervention period are the same for subjects in each arm. We standardized the visit schedule to control for any improvement in adherence, possible side effects which might result from VA/VD supplementation alone. We use several measures to assess VA/VD adherence: self-report, pill count, and nursing records of directly observed doses and returned pill boxes.

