### Planned statistical analyses

We hypothesize that effect of anti-TB and DM treatment in VA and/or VD arms will be better than the effect in the control arm. Descriptive statistics will be calculated and checked for balance in each arm in demographic, physical and other related measurements at baseline. Comparisons among the groups of pulmonary pathological damage, CD_4_^+^ T cell, HOMA-IR, etc., will be performed by Chi-square (categorical variables), F test (continuous variables, normal distribution) or Kruskal–Wallis H test (ranked data). Linear mixed-effects models will be used to analyze the main influencing factors.

We will also calculate anti-tuberculosis and diabetes treatment results, nutritional and immunologic indexes at three time points: before the supplementation (at the inclusion), 2 months after the supplementation, and at the end of the trial (6 to 8 months after the supplementation).

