## Discussion

To our knowledge, this study represents the first randomized controlled trial of a directly observed VA/D supplementation program in active pulmonary tuberculosis patients with diabetes that focused on the contribution of anti-TB and DM treatment effect and the possible mechanisms.

Tuberculosis and diabetes interact with each other, which might make clinical treatment become more difficult than the single disease of pulmonary tuberculosis or diabetes. As diabetes alters immunity to tuberculosis, longer times to culture conversion with treatment, and a higher rate of relapse might result. Treatment failure and death are more frequent in diabetic patients than patients with PTB alone. Alisjahbana reported that in patients with high adherence to treatment, 6-month sputum cultures were positive in 22.2% of patients with diabetes mellitus and in 6.9% of controls and these differences remained after adjustment for age, sex, body mass index, and other factors [15]. In a case–control study [16] treatment failure or death was seen in 41% of the patients with tuberculosis and diabetes mellitus, but in only 13% of those with tuberculosis alone. A recent study by Wang and colleagues [17] discovered that 1-year all-cause mortality was 17.6% in diabetic PTB patients versus 7.7% in non-diabetic controls, and death specifically attributable to pulmonary tuberculosis was significantly more common in diabetic patients (12.2% vs 4.2%).

The most important effector cells for containment of tuberculosis are phagocytes, monocytes and lymphocytes. Diabetes is known to affect chemotaxis, phagocytosis, activation, and antigen presentation by phagocytes in response to M tuberculosis. Vitamin A is an essential micronutrient for a variety of physiological processes, such as tissue differentiation, immunity, and vision. Also, the impacts of VA and retinoids on energy metabolism in animals and humans have been demonstrated in some basic and clinical investigations [18]. Also, it has been proposed recently that vitamin D play a critical role in immunity, respiratory health and insulin resistance. Vitamin A, its metabolites and vitamin D directly inhibit mycobacterial growth in culture [19].

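### Excluding patients found drug resistant during follow-up removes TB treatment failures after randomisation and biases the primary comparison

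*Protocol article*

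**What the plan says.** The protocol article, under Trial inclusion and exclusion criteria, opens its exclusion list with "Participants are excluded if they are unable or unwilling to provide informed consent" and continues with those who "are drug resistant at baseline or during the follow up". Pregnancy, lactation, recent use of steroids or supplements and renal failure follow in the same sentence.

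Under Baseline assessment the order of events is clear: "Following completion of the baseline assessment, participants receive their assignment to one of the four arms". Follow-up is therefore the time after assignment: "during the 24 to 32 weeks (according to the anti-tuberculosis drug treatment period) intervention period" (Visit schedule and measures), with outcomes taken at 2 months and at the end of the trial, 6 to 8 months in (Planned statistical analyses).

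The abstract states the primary outcome: "Our primary outcome measure is the efficacy of anti-tuberculosis treatment and ameliorating of glucose metabolism". The planned analyses are comparisons between groups. No analysis population is named, and no sentence says that a patient excluded for resistance after assignment is still followed or counted.

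**The concern.** An exclusion criterion should depend only on what is known, or fixed, before assignment. Resistance found during follow-up is neither. It is a route to treatment failure, and a patient who stays culture-positive still yields an isolate in which resistance can be found. The excluded patients will therefore tend to be those with a poor TB outcome.

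The supplements may also change who is excluded. The trial's own rationale, in Background and Discussion, is that vitamins A and D support the immune response to mycobacteria and inhibit their growth. If that is right, the arms may differ in how many patients reach the point of being labelled resistant.

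Three consequences follow. Failure is understated in every arm. A benefit that works by preventing these failures is partly or largely hidden. A false difference appears if resistance emerges, or is detected, at different rates in the arms. The lost patients also draw on the allowance from 84 to 100 per arm, which the article justifies by compliance, non-response and withdrawal and not by this exclusion.

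**Working it through.** The article gives no figure for this point, so there is none to reproduce. The calculation below shows what the rule does to a binary TB failure outcome.

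**Inputs**
- True failure on control, p = 22.2%. The Discussion reports from a cited study that "6-month sputum cultures were positive in 22.2% of patients with diabetes mellitus and in 6.9% of controls". It serves here as an illustrative rate; it is not the trial's planning value. A second illustration uses 41%, the failure-or-death figure cited in the same section.
- Share of failures excluded as resistant, q. The article does not give it; 10% to 50% is assumed.
- Sample size: 84 evaluable per arm (Sample size and power calculations). A factorial main effect compares two pooled arms with two, so 2 × 84 = 168 against 168.
- Two-sided 5% test of two proportions.

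**Formula.** If a share q of failures is dropped and all successes stay, the observed failure rate is p(1 − q)/(1 − pq).

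**1. True halving, 22.2% against 11.1%, same q in both arms**

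| q | control | vitamin | difference (points) | power, 168 v 168 | power after also removing the excluded |
|---|---|---|---|---|---|
| 0 | 22.2% | 11.1% | 11.1 | 78% | 78% |
| 10% | 20.4% | 10.1% | 10.3 | 75% | 74% |
| 25% | 17.6% | 8.6% | 9.1 | 69% | 68% |
| 50% | 12.5% | 5.9% | 6.6 | 56% | 52% |

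Example at q = 50%: 0.222 × 0.5/(1 − 0.111) = 0.111/0.889 = 12.5%.

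For a comparison of two single arms of 100, power falls from 55.9% to between 52.2% (q = 10%) and 34.4% (q = 50%). With 41% halved to 20.5%, it falls from 88.7% to between 86.2% and 67.7%.

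**2. No true effect, q differs between arms**
- 22.2% in both, q = 25% against 50%: 17.6% against 12.5%, a false difference of 5.1 points.
- 22.2% in both, q = 10% against 30%: 20.4% against 16.6%, or 3.8 points.
- 41% in both, q = 10% against 30%: 38.5% against 32.7%, or 5.8 points.

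Swapping the shares reverses the sign. The odds of failure in an arm are multiplied by (1 − q), so the odds ratio is biased by the ratio of these factors. For 25% against 50% that is 0.50/0.75 = 0.67, although the true value is 1.

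**3. The supplement prevents half of the failures that would be labelled resistant, and no others**
- p = 22.2%, 30% of control failures resistant: the true rates are 22.2% and 18.9% (3.3 points). The observed rates are 16.6% and 16.1% (0.6 points).
- p = 22.2%, 50% resistant: the true rates are 22.2% and 16.65% (5.55 points). The observed rates are 12.5% and 11.8% (0.7 points).

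Most of a real benefit vanishes in this case.

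**4. Patients lost.** 100 × p × q gives 2 to 11 per 100 control patients at p = 22.2%, and 4 to 21 at p = 41%, for q = 10% to 50%. The whole allowance is 100 − 84 = 16 per arm.

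**The case against.** The strongest reply has four parts.

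- **The word is ambiguous.** Exclusion could mean only stopping the supplement, and a full protocol or analysis plan may define the analysis set. However, the phrase stands in the trial's eligibility list beside consent and pregnancy, where removal from the trial is the plain reading, and nothing in the article counters it. If retention was intended, the wording still has to change.
- **Part of what the phrase covers is legitimate.** It could include resistance already present at entry whose test result arrives late. Excluding those patients is acceptable if the specimen predates assignment and the decision is made blind to arm. The wording does not limit itself to that case.
- **Equal exclusion shares do not bias every measure.** This is correct. In the first table the odds ratio stays at 2.29 for every q, and the risk ratio moves slightly away from 1 (2.00 to 2.12). The Discussion mentions logistic regression, which estimates odds ratios. In that scenario the shrinkage is confined to the risk difference, with a loss of events and power. The protection fails when shares differ by arm or when the vitamins act on the failures that would be labelled resistant (steps 2 and 3).
- **The figures are hypothetical.** This also stands. The article states neither a binary culture endpoint nor a factorial main-effect test as primary, nor any rate of resistance or when it is tested for. At q = 10% the cost is modest. The spurious example needs a gap between arms for which the article offers no evidence. The glucose outcome is not covered by this calculation.

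These limits concern the size of the bias. They do not remove the flaw, and if excluded patients are not followed, neither size nor direction can be established later.

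**Conclusion.** The criterion is wrong as written. It makes a post-randomisation event, closely related to a primary outcome and possibly affected by treatment, a reason for exclusion. Following it would break the randomised comparison for TB treatment efficacy.

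The conclusion rests on the text and the order of events, together with the plain reading of exclusion as removal from the trial. It does not depend on the illustrative figures. Those figures show that the effect could range from a few points of power to the loss of most of a real benefit, or to a false difference of about 4 to 6 points in the cases shown, in either direction. They assume a binary failure outcome at 22.2% or 41% and excluded shares between 10% and 50%.

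This must be fixed before enrolment goes further: the article reports 37 of a planned 400 patients enrolled, and outcomes of dropped patients may not be recoverable.

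**What to change.** - Limit the resistance criterion to resistance shown in a specimen taken before randomisation. A result that arrives later may still count, provided the decision is made without knowledge of the arm. Remove the reference to follow-up from the eligibility list.
- State that every randomised patient in whom resistance emerges or is found later stays in the assigned arm, is followed to the final visit, and is counted with the TB outcome observed. Specify in advance how resistance found in follow-up enters that outcome.
- Report the number found resistant after randomisation by arm, and present the analysis without them only as a sensitivity analysis.
- If the phrase was also meant to govern stopping the supplement or changing treatment, put that in a separate clinical section. This point takes no position on that care; it concerns only follow-up and analysis.

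The cost is a one-phrase eligibility amendment, a sentence on the analysis set, and follow-up of the patients who would otherwise have been dropped, at visits that already exist. Any patient already excluded under the present wording should be traced and reinstated for analysis.

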### Approvals and data safety and monitoring

The trial was approved by Ethics Committee of the affiliated hospital of Medical College of Qingdao University. All participants provide written informed consent. Besides of VA and/or VD supplementation, we are giving nutritional and behavioral suggestion and instruction that is highly integrated with normal clinical care to all the subjects. Also, we established a data safety and monitoring plan, which requires interim analyses after every twenty patients are enrolled.

### Recruitment

Medical providers in the four TB clinics are asked to invite all patients initiating on-site anti-TB and DM treatment to consider enrolling in the trial. Subjects also are referred by other subjects or through the project group. The initial steps in subject recruitment include a brief screening survey, informed consent, and in depth verification of eligibility using medical records and discussion with providers.

